### Study measures

#### Primary outcomes

The primary study outcomes will be derived from the variables coded (Table 4) using recorded conversations that parents and teens had when engaging in the simulator and naturalistic drives.

Once reliable, study team members will code whether parents identify the hazard, whether the parent verbally identifies roadway hazards, if hazard identification uses a hazard anticipation communication (i.e., higher-order communication), if instruction precedes or follows the hazard event, if the hazard anticipation communication includes elements of motivational interviewing, and how many times parents provide functional driving instructions. Hazard anticipation communication, a form of higher-order driving instruction that can be applied more generally to driving (e.g., “When there are brake lights ahead, you should be ready to brake too.”), will be coded when parents indicate why the hazard is dangerous by causally connecting dangerous features and their potential outcomes. Functional instruction will be coded for instruction that applies only to the current context (e.g., “Slow down.”). We will also code whether the teen verbally identifies the hazard via hazard anticipation communication or by only pointing out the hazard and if identification precedes or follows the hazard event. Measures will be captured for each hazard that is presented in the simulator drive for a total of 17 repeated measures per dyad. For each of the 17 scenarios embedded in the simulator drive, a binary indicator reflecting presence or absence will coded for hazard anticipation communication, its sub codes, and hazard identification only. The number of functional driving instructions produced by the parent per hazard scenario will be recorded as a count.

Unlike simulator drives, hazards encountered in during naturalistic driving are not standardized. Therefore, coding will focus on general hazard anticipation patterns rather than per-hazard responses. Raw counts of each conversational measure will be recorded. because drives varied in length (10–30 min), counts will be modeled as a rate per 10 min of drive time. Each dyad contributed four naturalistic drives.

##### Coding procedures and reliability

Coding will follow an established coding scheme, informed by prior work on parent-child safety and parent-teen driving conversations (e.g [8, 16, 17]), . Two trained research assistants will code approximately 20% of transcripts to obtain interrater reliability. Coders will achieve substantial agreement as indicated by Cohen’s kappa statistic of 0.61 or higher for bivariate variables and an ICC of 0.75 or higher for continuous variables.

**Table 4 Tab4:** Primary and secondary measures, operationalized, and coding scheme per data source

Outcome Variables	Measure/Operationalization	Simulator Drive Coding	Naturalistic Drive Coding
**Primary Outcomes**			
Hazard Anticipation Communication (HAC)	Higher-order communication that helps drivers identify and respond hazards by pointing out why they are critical and the clues on the roadway you can use to identify them. (e.g., “There could be something in front of the bus that we can’t see. They could pop out without warning.”)	Presence/Absence	Count
Before hazard	If HAC is present, does the HAC occur before or after the hazard would become critical if no action were taken	Presence/Absence	Count
Motivational interviewing	If HAC is present, are elements of motivational interviewing present in parent’s HAC?	Presence/Absence	Count
Functional Driving Instruction	Driving instruction related to vehicle handling and navigation (e.g., “Slow down.”, “Check your speed.”)	Count	Count
Hazard Identification Only	Identification of the hazard without any additional context or instruction (e.g., “I see a pedestrian.”, “That car is braking.”)	Presence/Absence	Count
**Secondary Outcomes**			
Risky Driving Events	Hard braking, speeding, hard accelerator press	Count	-
Lane Change	Occurs when the center of the participant vehicle crossed a lane boundary.	Presence/absence	-

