Parents joined their teens in the simulator cab after the teen completed the acclimation drive. As before, parents were in the front passenger seat. Prior to the start of the study drive, teens also completed the wellness survey. The teen and parent then completed the study drive, which lasted approximately 20 min. The study drive followed a similar route as the acclimation drive. The drive started in a downtown area, went through a residential neighborhood, followed by a rural area, and completed in a residential town. Unlike the acclimation drive, the study drive included a variety of typical roadway conditions and 17 potential hazard scenarios (Table 2). Note that no hazards evolved into critical driving events that would result in a crash. Full descriptions of each hazard event can be found in a previous report [12]. Some of the simulated hazards were direct reflections of hazards covered by HazAPP, whereas others represented novel hazards. Parents and teens were not given explicit instructions to communicate during the drive but were encouraged to treat it like an ordinary driving session. The experimenter was able to communicate with participants through a speaker installed in the cab as needed. Parent-teen verbal communication during the drive was captured using both audio and video for subsequent coding. At the conclusion of the drive, participants remained seated in the vehicle until the experimenter safely terminated the simulation. Before leaving the simulator, the parent and teen completed post-drive wellness questionnaires. After leaving the simulator, the parent and teen concluded the visit by returning the dashcam and completing payment forms.

**Table 2 Tab2:** List of hazard scenarios included in study drive

Hazard Type	Traffic environment		
	Downtown	Residential	Rural
**Path Conflict**	Left lane impeded	Partial lane obstruction	
**Stopping Vehicles**	Platoon braking	Intermittent braking	Lead vehicle
**Roadside Incursions**	Parallel parked car	School zone Potential vehicle incursion	Deer
**Forced Path Change**	Work zone lane closure	Lane drop	
**Obscured Potential Hazards**	Obscured cross traffic Mid-block crosswalk	Obscured T-intersection 90% curve	
**Emergency Vehicles**	Ambulance	Fire station	

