#### Secondary outcomes

Secondary outcomes will focus on teens’ driving performance in the simulator. More specifically, simulator data will be reduced to capture risky driving events, changes to lane position, and lane changes in response to hazards and parental instruction. Risky driving events will include hard braking events, rapid acceleration, and speeding. Additionally, we will capture lane changes in response to hazards and parents’ instruction. Parental hazard anticipation communication is expected to prompt teens to adjust their speed and lane position proactively when approaching hazards, resulting in fewer hard braking events and more appropriate lane changes. These measures will be captured for each of the embedded hazards.

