##### Secondary analysis

The secondary set of analyses will examine any changes to teen’s driving behavior in response to parental instruction during the simulator drive. More specifically, we will use mixed-effects models to predict outcomes of risky driving behaviors and lane changes. Each model will include a fixed effect of condition and covariates detailed above. Potential random effects of participant and hazard scenario will be determined using loglikelihood ratio testing. P-value adjustments for multiple tests will be undertaken. We expected that teens of parents in the intervention arm of the study will exhibit improved driving responses to potential hazards in the simulator drive.

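### Lane change is coded as present or absent with one condition effect over all hazards, but the hypothesis is about appropriate lane changes, so the sign of the effect does not show benefit or harm

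*Protocol article*

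**What the plan says.** Four places in the protocol article bear on this outcome.

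- **Table 4, Secondary Outcomes.** A lane change "Occurs when the center of the participant vehicle crossed a lane boundary". The simulator coding is "Presence/absence". The row does not mention direction, timing or appropriateness, and does not say whether presence is the favourable value.
- **Secondary outcomes.** Lane changes are to be captured as responses to hazards and to what the parent says. The expected effect of better parental communication is described as "resulting in fewer hard braking events and more appropriate lane changes". On the unit of measurement: "These measures will be captured for each of the embedded hazards".
- **Visit 2 and Table 2.** The study drive has "17 potential hazard scenarios". They include forced path changes, such as "Work zone lane closure", alongside stopping vehicles, roadside incursions, obscured hazards and emergency vehicles. Full scenario descriptions are said to be in a previous report.
- **Secondary analysis.** The article states that "we will use mixed-effects models to predict outcomes of risky driving behaviors and lane changes". It adds: "Each model will include a fixed effect of condition and covariates detailed above". Random effects of participant and hazard scenario are candidates, to be chosen by likelihood ratio testing. The expectation is that teens in the intervention arm respond better to hazards.

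**The concern.** The measure does not carry the property that the hypothesis is about. The prediction concerns appropriate lane changes, but the code records only whether a boundary was crossed. Where the road forces a path change, presence is presumably the good result. Where the task is to slow for a vehicle ahead, presence is not obviously good and may be bad. A single condition coefficient over both kinds of scenario averages effects for which benefit can have opposite signs.

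Two things are at stake. A positive or negative coefficient could not be read as better or worse driving. And an intervention that improved lane behaviour in every scenario could produce a result close to null.

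**Working it through.** **1. The plan's own figure.** Counting Table 2 by hazard type: path conflict 2 + stopping vehicles 3 + roadside incursions 4 + forced path change 2 + obscured hazards 4 + emergency vehicles 2 = 17. This reproduces the stated number of scenarios.

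**2. Hypothesis against measure.** The Secondary outcomes section needs a variable that rises when a lane change is made where it should be and does not rise when one is made where it should not be. The Table 4 variable rises in both cases. Table 4 does qualify another outcome in this way: hazard anticipation communication has sub-codes for timing and for motivational interviewing. Lane change has none.

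**3. Whether the model repairs it.** A random hazard intercept would absorb different baseline crossing rates but would not turn the outcome so that higher means better. A random condition slope by hazard, which the text neither specifies nor rules out, would show heterogeneity, but its mean would still be an average of unoriented effects.

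**4. Cancellation, simple illustration (all rates and the 4/13 split are assumed).** Suppose 4 scenarios call for a lane change and 13 do not. Where called for, lane changes rise from 60% to 80%. Where not, crossings fall from 10% to 4%. Both are improvements.

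- Control: (4 × 0.60 + 13 × 0.10)/17 = 3.70/17 = 21.8%
- Intervention: (4 × 0.80 + 13 × 0.04)/17 = 3.72/17 = 21.9%

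Adjusting for scenario does not help. The odds ratio is (0.80/0.20)/(0.60/0.40) = 2.67 in the first class and (0.04/0.96)/(0.10/0.90) = 0.375 in the second, which are reciprocals. The Mantel-Haenszel odds ratio stratified by scenario is

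(4 × 0.80 × 0.40 + 13 × 0.04 × 0.90)/(4 × 0.20 × 0.60 + 13 × 0.96 × 0.10) = (1.28 + 0.468)/(0.48 + 1.248) = 1.01.

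**5. Range over other assumptions.** Let k be the number of scenarios that call for a lane change. Lane changes where called for rise from 60% to 75%; crossings elsewhere fall by one of two amounts. Expected crossings per drive = k × p(called for) + (17 − k) × p(not called for). For example, k = 4 with 15% to 10% gives 2.40 + 1.95 = 4.35 in control and 3.00 + 1.30 = 4.30 in the intervention arm.

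The odds ratios and power come from a simulation with 51 dyads per arm (102 completers, assumed evenly split), a dyad random intercept with SD 0.5, and 300 replicates. The model was logistic with one condition effect, adjustment for scenario class and dyad-clustered standard errors, tested at two-sided 5%. It stands in for the planned mixed model.

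| k | Crossings where not called for | Per drive, control v intervention | Odds ratio as coded | Power as coded | Power if scored appropriate yes/no |
|---|---|---|---|---|---|
| 2 | 20% to 12% | 4.20 v 3.30 | 0.69 | 67% | 100% |
| 2 | 15% to 10% | 3.45 v 3.00 | 0.79 | 32% | 92% |
| 4 | 20% to 12% | 5.00 v 4.56 | 0.84 | 21% | 100% |
| 4 | 15% to 10% | 4.35 v 4.30 | 0.98 | 7% | 97% |
| 5 | 20% to 12% | 5.40 v 5.19 | 0.92 | 10% | 100% |
| 5 | 15% to 10% | 4.80 v 4.95 | 1.05 | 6% | 99% |
| 8 | 20% to 12% | 6.60 v 7.08 | 1.14 | 14% | 100% |
| 8 | 15% to 10% | 6.15 v 6.90 | 1.28 | 34% | 100% |

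Every row is an improvement in every scenario, yet the odds ratio falls on both sides of 1.

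**6. Exact cancellation in expected counts.** A 15-point rise where called for is offset by a fall elsewhere of k × 15/(17 − k) points: 2.0 (k = 2), 4.6 (k = 4), 6.3 (k = 5) or 13.3 (k = 8).

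**The case against.** The best reply is that Table 4 gives only the rule for detecting a lane change in the simulator signal, while the Secondary outcomes section supplies the rest: the change must be a response to a hazard or to the parent's words, and appropriateness is the stated expectation. The scenario-by-scenario rules would then belong to the data reduction, which an article need not print. The first part stands to this extent: the response condition narrows which crossings count. But an unsuitable manoeuvre can also be a response, so it does not orient the outcome. The second part would answer a complaint about missing detail. The point here is that a stated coding and a stated model do not match a stated hypothesis.

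It is also fair that Table 2 gives names only, without lane counts or road geometry. A reader might infer that a crossing at platoon braking, lead vehicle, the curve or the school zone is a swerve or lane departure. The documents do not say so, and a planned lane change away from braking traffic could be suitable. Only the forced-path-change labels carry a clear implication, so the number of scenarios in each class is unknown. Likewise, a reader might infer that the model contains only a hazard intercept; the text leaves the form of the random effects open.

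Finally, a reader might extend the criticism to risky driving events. That does not hold. Table 4 does not say that hard braking, speeding and hard acceleration are summed, and fewer is better for all three.

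**Conclusion.** The point holds for the lane-change outcome. Followed as written, the condition coefficient has no direction of benefit, and improvements in both kinds of scenario can cancel. How far they would cancel depends on the crossing rates and the scenario mix, neither of which the documents give. Under the assumed rates above, the pooled odds ratio runs from 0.69 to 1.28 and power from 6% to 67%, against 92% to 100% when the same data are scored for appropriateness. A near-null result is one possibility among these, not the expected one.

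A reader might go further and infer that the trial cannot tell whether teens drove better. The documents do not support that. Risky driving events are a separate secondary outcome with a clear direction, and the primary communication outcomes do not depend on lane changes. The consequence is confined to what can be concluded from lane change, which is worth correcting but does not threaten the trial's main question.

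**What to change.** Before the simulator data are reduced, and blind to arm, use the existing scenario descriptions to classify each of the 17 scenarios as lane change called for or not called for. Then take one of two routes, fixed in advance:

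- analyse two outcomes: lane change made where called for (higher is better), and boundary crossing where not called for (lower is better); or
- score each scenario as appropriate response yes or no, and keep a single model.

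The Driving performance section describes data reduction as still to come, so the classification can be made before results by arm are seen.

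The cost is a 17-row table and, under the first route, one extra model and one more test within the multiplicity adjustment already planned. Each of the two outcomes uses fewer scenarios, so its precision is somewhat lower. The power in the last column of the table applies to the second route; the first was not simulated.

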#### Secondary outcomes

Secondary outcomes will focus on teens’ driving performance in the simulator. More specifically, simulator data will be reduced to capture risky driving events, changes to lane position, and lane changes in response to hazards and parental instruction. Risky driving events will include hard braking events, rapid acceleration, and speeding. Additionally, we will capture lane changes in response to hazards and parents’ instruction. Parental hazard anticipation communication is expected to prompt teens to adjust their speed and lane position proactively when approaching hazards, resulting in fewer hard braking events and more appropriate lane changes. These measures will be captured for each of the embedded hazards.

#### Other measures

Parents completed a set of questionnaires via Qualtrics during Visit 1, including demographics (i.e., race/ethnicity, educational background, and household income) and the Early Adolescent Temperament Questionnaire (Ellis [18]), . Additionally, questionnaires assessed parents’ driving safety beliefs, approach to and experiences with their teen while providing driving instruction, their typical communication style while supervising practice drives, and parents’ perspectives on their teen’s readiness to drive. These responses will be used to characterize the sample and to contextualize observed parent-teen communication during the simulator session. Teens also completed questionnaires via Qualtrics during Visit 1. These questionnaires included information about driving experience (i.e., permit date, driver education engagement, and frequency of recent driving exposure) and how often their parent discussed various driving topics during supervised practice. Teens also reported on their perceptions of their parent’s communication style using the Family Communication Pattern Scale – Revised [19] and the Parental Authority Questionnaire [20]. These measures will provide context for interpreting the in-drive communication recorded at Visit 2.

### Analytic plan

#### Data management

Participants were identified by number rather than by name. The master list linking participant IDs to participants identifiable information was saved on a password-protected data server accessible only to Institutional Review Board (IRB) approved members of the research team.

#### Questionnaire data

All questionnaire data collected from teens and parents are saved in a password-protected Qualtrics database. Study team members checked questionnaire data regularly for completeness. At the end of data collection, all questionnaire responses were downloaded and saved to a password-protected data server accessible only to IRB-approved members of the research team. These data were then cleaned and, where appropriate, coded for later analysis.

#### Simulator data

##### Video

Audio and video recordings of the hazard-laden simulator drives were transferred from the simulator hard drive to a password-protected data server accessible only to IRB-approved members of the research team. Files were checked once per week to ensure they were transferred without error. Researchers also made notes regarding any noteworthy events that occurred during the study drive. Audio from the video files will be used to generate verbatim transcripts for parent-teen conversations for later coding. Transcription will be conducted using University licensed AI, ensuring the protection of participant confidentiality.

##### Driving performance

Driving performance data gathered during the hazard-laden simulator drive were housed in a password-protected database managed by the Driving Safety Research Institute, home of the simulator used for data collection. Study team members ensured these data were properly transferred after each study visit. These data will be reduced for later analyses.

#### Naturalistic driving data

Audio and video recordings of the four naturalistic drives, captured by parents as they instructed their teens while driving on real roads, were downloaded from the camera’s memory card at the conclusion of the second study visit. Videos were checked for quality and completeness. In most cases, drives were separated into smaller video files by the DJI Action II camera. Study team members checked the videos and merged files chronologically to ensure that each of the four naturalistic drives were accessible as a single video file. Study team members also recorded noteworthy events and data quality issues (e.g., camera malfunctions). These videos will be transcribed verbatim in a similar manner as the simulator drives. Transcription of naturalistic video files will be conducted using Whisper AI and then imported to ELAN. Whisper AI can be run on a computer’s hard drive, ensuring participant privacy. Transcriptions will be coded in ELAN for later analysis.

#### Missing data

Missing data will be addressed to minimize bias and protect statistical power. To address missing data, we will begin by examining patterns of missingness. If rare, missing values will be assumed to be unrelated to study outcomes or relevant covariates and will be treated as if missing completely at random. We will proceed with analyses that ignore those observations. However, if missingness is deemed systematic or related to key variables, we will use a multiple-imputation approach, applying a simulation-based method grounded in a model that represents the missing data mechanism [21, 22].

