#### Planned data analysis

##### Descriptive analysis

Data analysis will address our main hypothesis that parents who engage in the training will exhibit improved communication about potential hazard detection with their teens compared to those in the control condition. All analyses will include covariates of relevant demographic (e.g., sex, race/ethnicity) and driving related covariates (e.g., driver education engagement, duration of licensure, family communication patterns, etc.). P-value adjustments will be made as necessary.

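### The missing-data rule ties missing completely at random to rarity and, by implication, drops dyads with complete outcomes when one baseline covariate is missing

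*Protocol article*

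**What the plan says.** The Missing data section sets out three steps. First, "we will begin by examining patterns of missingness". Second, "If rare, missing values will be assumed to be unrelated to study outcomes or relevant covariates and will be treated as if missing completely" (that is, MCAR), followed by "We will proceed with analyses that ignore those observations". Third, "if missingness is deemed systematic or related to key variables, we will use a multiple-imputation approach". The section gives bias reduction and preservation of power as its aims. It puts no figure on rare and does not separate missing outcomes from missing covariates.

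The Descriptive analysis section adds: "All analyses will include covariates of relevant demographic (e.g., sex, race/ethnicity) and driving related covariates". The examples there are sex, race/ethnicity, driver education, duration of licensure and family communication patterns, and the list is left open. The Primary analysis section carries these covariates into both the simulator and the naturalistic models, and the Secondary analysis section does the same for driving performance.

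On the outcome side, the Primary outcomes section has each hazard coded "for a total of 17 repeated measures per dyad" in the simulator and states: "Each dyad contributed four naturalistic drives".

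**The concern.** Rarity is a quantity and missing completely at random is a mechanism, so the first cannot establish the second. The sound argument for setting aside a few missing values is that they can do little harm whatever their cause. The section does not make that argument.

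The two branches also do not divide the cases cleanly. Missingness that is rare and systematic satisfies both. Missingness that is frequent but shows no pattern satisfies neither. The preliminary look at patterns will seldom settle the first case: 1-3% of 102 dyads is one to three dyads, too few to reveal a cause. In practice the rare case will tend to end in deletion.

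Deletion matters most for covariates. A dyad-level covariate sits on every row of that dyad, so one unanswered item can remove a dyad whose recordings are complete. That gives up precision and works against the section's own aim of preserving power. The set of dyads analysed would also depend on which covariates are finally chosen.

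**Working it through.** **Benchmark in the plan.** The Missing data section states no figure. The nearest is the Sample size section's minimum of 100 dyads for 0.80 power; the Study population section reports 102 completing dyads. The margin is two dyads, so losing three goes below the stated minimum. The minimum is given without a numeric effect size or sidedness, so no power loss is derived from it here.

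**Outcome records.** A missing hazard record or drive is one row. A likelihood-based mixed model keeps the dyad's other rows and is valid under missing at random. Ignoring the missing row is the same computation as handling it under missing at random; only the stated assumption is stronger than needed.

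Rarity does limit the damage. Let an arm's true proportion be p and the share missing m. The worst-case biases in the observed proportion are:
- all missing values are events: (p − m)/(1 − m) − p
- no missing value is an event: p/(1 − m) − p

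With p = 0.30 (assumed):
- m = 1%: 0.29/0.99 − 0.30 = −0.007, and 0.30/0.99 − 0.30 = +0.003
- m = 2%: 0.28/0.98 − 0.30 = −0.014, and 0.30/0.98 − 0.30 = +0.006
- m = 5%: 0.25/0.95 − 0.30 = −0.037, and 0.30/0.95 − 0.30 = +0.016

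**Baseline covariates.** Inputs:
- 102 dyads (Study population).
- 17 simulator records and 4 drives per dyad (Primary outcomes).
- k = 4 covariates that could be missing. Five are named, but sex is the randomisation stratum and is reported for all 102 teens (52 + 50).
- m = 1-3% missing per covariate, independently across covariates. This is an assumption; the document gives no rate.

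Share of dyads with at least one missing covariate = 1 − (1 − m)^4.

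| m | Share lost | Dyads lost of 102 | Simulator records (×17) | Drives (×4) |
|---|---|---|---|---|
| 1% | 1 − 0.9606 = 3.9% | 4.0 | 68 | 16 |
| 2% | 1 − 0.9224 = 7.8% | 7.9 | 135 | 32 |
| 3% | 1 − 0.8853 = 11.5% | 11.7 | 199 | 47 |

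If instead the same dyads lack all four covariates, the loss is only m × 102, or about 1 to 3 dyads.

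**The case against.** The best defence is that the rule is a working approximation. Rare values are to be treated as if completely random, patterns are inspected first, and multiple imputation is available when missingness looks systematic. The worst-case figures support the practical side of this: with 1% missing, the bias in an arm's proportion stays under 0.01. For outcome rows the defence stands, and only the wording needs correcting.

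A second defence is that the loss is probably small. Questionnaires were completed on site and checked regularly for completeness, 102 of 103 dyads finished all procedures, and unanswered items often cluster in the same people. This also stands, and it puts the likely loss at or below the low end of the range.

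A third is that covariate handling is commonly left to an analysis plan that is not shown. That would answer a complaint of omission, but the article states a rule, and the rule as stated leads to deletion.

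Four stronger readings are tempting, and the document does not support them:
- A reader might take it that the plan says dyads are dropped for a missing covariate. It speaks only of observations; the loss of dyads follows from covariates that are constant within dyad and present in every model.
- A reader might conclude that systematic missingness is not provided for. The multiple-imputation branch provides for it.
- A reader might infer bias between arms. Parents answered before learning their assignment and teens before HazAPP was used (Data collection, Visit 1), so the programme cannot have caused missing baseline answers.
- A reader might put a number on lost power or assume a much larger loss. That would need more covariates than the document names and a simple comparison of one value per dyad, which is not the planned analysis.

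**Conclusion.** The concern holds as a minor point. The sentence deriving missing completely at random from rarity is unsound, and the two branches overlap for rare but systematic missingness. For outcome records the consequence is close to nil. For baseline covariates, applying the rule implies losing dyads with complete outcomes, at a cost in precision rather than validity of the arm comparison. The estimate of about 4 to 12 of 102 dyads rests on four covariates, 1-3% missing in each, and independence between them. Clustering or nearly complete questionnaires would make it smaller; further covariates from the open list could make it larger.

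**What to change.** Replace the rule with four statements:
- Every randomised dyad with outcome data is analysed in its assigned arm.
- Missing outcome records are treated as missing at random through the mixed-model likelihood.
- A dyad with a missing baseline covariate is kept by simple imputation whatever the frequency: the mean for a continuous covariate, a missing category for a categorical one.
- Multiple imputation that includes arm, sex and outcome is run as a sensitivity analysis.

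The sentence that infers completely random missingness from rarity is deleted, and no threshold for rare is then needed. The article describes outcome coding and analysis as still to come, so the change can be made beforehand. The cost is a few sentences and minor programming.
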